## Abstract

**Background:**

Long COVID is a serious public health concern due to its high prevalence and potentially debilitating symptoms. Symptoms may include fatigue, dyspnea, cognitive problems, insomnia, anxiety, and depression. There is currently no cure for long COVID, and the average length of recovery and proportion of patients who fully recover are still unknown. Subsequently, there is a critical need to improve function. Research in other chronic conditions suggests that psychosocial self-management interventions reduce symptom severity and interference with functioning. We describe the design of our study to examine the feasibility, acceptability, appropriateness, and preliminary efficacy of an intervention designed to improve symptom management and coping in adults with long COVID.

**Methods:**

This pilot trial (*N* = 50) uses a pragmatic, randomized two-group parallel design set within the University of Washington Post-COVID Rehabilitation and Recovery Clinic. The self-management intervention is a 6-week, group-based telemedicine intervention that teaches evidence-based strategies to manage common symptoms and improve stress management as well as communication and self-advocacy. The comparator is a wait-list control. Participants complete self-report measures of the primary and secondary outcomes at baseline and post-treatment/wait-list. Primary outcomes include intervention feasibility, acceptability, and appropriateness. Secondary outcomes include Patient-Reported Outcomes Measurement Information System measures of fatigue, sleep disturbance, cognitive difficulties, self-efficacy, pain interference, depression and anxiety symptoms, and a measure of long COVID symptoms and impression of change. At post-intervention, intervention participants also complete a qualitative interview to inform intervention refinement. Quantitative data will be examined using descriptive and statistical analysis including *t*-tests and chi-square tests to compare the intervention and wait-list groups on secondary outcomes. Qualitative data will be analyzed using the rigorous and accelerated data reduction technique (RADaR).

**Discussion:**

Results of this pilot randomized controlled trial will characterize the feasibility, acceptability, and appropriateness of the self-management intervention and inform intervention refinement necessary prior to further testing. Long COVID is a public health concern, and rehabilitation approaches that equip patients to manage symptoms may improve patient function and quality of life and reduce burden on the health care system.

**Trial registration:**

NCT05658536. December 16, 2022.

**Supplementary Information:**

The online version contains supplementary material available at 10.1186/s40814-024-01515-2.

## Introduction

The World Health Organization defines long COVID as “the continuation or development of new symptoms three months after the initial SARS-CoV-2 infection, with these symptoms lasting for at least 2 months with no other explanation” [1]. Long COVID poses a serious public health concern as 1 in 13 American adults report experiencing long COVID symptoms [2]. People with long COVID can present with a variety of symptoms ranging from mild to debilitating in severity. Some of the most common and disabling symptoms include fatigue, dyspnea, cognitive problems, pain-related symptoms, and insomnia. In addition, many adults with long COVID report anxiety and depression [3, 4].

Compared to other chronic health conditions, long COVID is new and subsequently less researched. There is currently no known cure for long COVID, and the average length of recovery as well as the proportion of patients who fully recover is still unknown. Given the variability and chronicity of long COVID symptoms, there is a critical need for intervention research to improve symptom management and functioning. Psychosocial self-management interventions could be particularly beneficial for targeting the various biopsychosocial factors that influence long COVID symptoms as well as the distress associated with living with variable symptoms and a relatively novel health condition [5]. Self-management has been defined by Barlow and colleagues [6] as “the individual's ability to manage the symptoms, treatment, physical and psychosocial consequences and life style changes inherent in living with a chronic condition.” Self-management is considered a valuable approach for the management of complex chronic illness and multiple morbidity. For example, self-management is one of four goals in a strategic framework for improving the health status of people with multiple chronic conditions published by the Department of Health and Human Services [7]. Research on patient populations with similar symptom profiles as long COVID (e.g., myalgic encephalomyelitis/chronic fatigue syndrome, multiple sclerosis) suggests that psychosocial interventions focused on self-management can reduce symptom severity and interference with functioning and improve coping [8, 9].

Self-management interventions equip and empower people with chronic health conditions and/or disability to actively manage their symptoms by providing them with strategies that they can use in their day-to-day lives [10, 11]. For example, these strategies may include pacing and energy conservation to reduce or manage fatigue and pain, practicing breathing exercises to improve shortness of breath and related anxiety, applying attention strategies to improve cognition, using cognitive behavioral techniques to change unhelpful patterns of thinking, enlisting social support to improve coping, engaging in goal-directed behavior aligned with values to improve mood, participating in mindfulness and relaxation practices to reduce stress and support mood, and improving sleep hygiene to optimize sleep, to name a few [12]. Furthermore, telemedicine is a viable platform for delivering self-management interventions [13]. Telemedicine is convenient, accessible, and cost-effective, has high patient satisfaction ratings, and reduces the risk for transmission of COVID-19 [14–16].

The mixed-methods randomized controlled trial (RCT) described here was developed in response to the critical need to advance research on effective psychosocial rehabilitation for adults with long COVID. We describe a pragmatic, randomized two-group parallel design to examine the feasibility, acceptability, and appropriateness and explore the preliminary efficacy of a 6-week telemedicine self-management group intervention for adults with long COVID. The self-management intervention will be compared to a wait-list control condition (delayed treatment) because there is currently no standard rehabilitation intervention for adults with long COVID.

Based on the National Institutes of Health (NIH) Stage Model of Behavioral Intervention Development [17], this pilot RCT is consistent with Stage 1 research activities focused on pilot testing and refining the intervention. Specifically, this is the first trial in a program of research aimed at developing and optimizing a psychosocial self-management intervention for adults with long COVID. The intervention is based on evidence-based self-management treatments for other rehabilitation patient populations (e.g., multiple sclerosis) and is already being delivered at the University of Washington (UW) due to high need and demand. Nevertheless, an iterative multistage approach is necessary to test and refine the intervention to be maximally effective and implementable in the intended treatment setting [17]. This pilot RCT is also pragmatic in that it is being conducted and evaluated in the intended treatment setting — an overburdened long COVID clinic in an academic medical center (AMC) setting with AMC providers.

This pilot RCT has three aims designed to inform the overall goal of intervention refinement. The first aim is to examine the feasibility, acceptability, and appropriateness of a telemedicine group self-management intervention designed to improve symptom management and coping in adults with long COVID. We hypothesize that the intervention will demonstrate feasibility, acceptability, and appropriateness, and that average session attendance will be comparable to attendance in RCTs of psychosocial interventions in other rehabilitation populations (43–93%; [18, 19]). The second aim is to explore the preliminary efficacy of the intervention for improving long COVID symptoms. We hypothesize that intervention participants will report greater pre- to posttreatment improvements in long COVID symptoms and psychosocial outcomes as compared to wait-list participants. The third aim is to use qualitative data from interviews with intervention participants to understand their perceptions of the feasibility, acceptability, appropriateness, and perceived efficacy of the intervention to improve the intervention. We do not have a priori hypotheses regarding intervention participant feedback.

## Methods

### Study design overview

This pilot trial uses a pragmatic, randomized two-group parallel design to examine the feasibility, acceptability, appropriateness, and preliminary efficacy of a 6-week telemedicine group self-management intervention for adults with long COVID. The intervention is aimed at improving symptom management and coping in adults with long COVID. Participants are randomized to the intervention group or a wait-list control group. All study methods and procedures have been approved by the UW Institutional Review Board (IRB). The trial is registered on ClinicalTrials.gov with the identifier: NCT05658536. See Table 1 for SPIRIT flow diagram for participant timeline. See supplementary table for SPIRIT Checklist.

**Table 1 Tab1:** Schedule of enrollment, interventions, and assessments (SPIRIT 2013 guidelines)

	**Study period**		
	**Enrollment**	**Allocation**	**Post-allocation** **6 weeks (post-treatment/wait-list)**
**Timepoint**	***-t***_***1***_	**0**	***t***_***1***_
**Enrollment**			
** Eligibility screen**	X		
** Informed consent**	X		
** Allocation**		X	
**Conditions**			
*** Telemedicine self-management group***		X	
*** Wait-list control***		X	
**Assessments**			
** Primary outcomes**			
Acceptability of Intervention Measure [20]			X*
Intervention Appropriateness Measure [20]			X*
Feasibility of Intervention Measure [20]			X*
** Secondary outcomes**			
Depression Short Form 8b** [21]		X	X
Anxiety Short Form 8a** [21]		X	X
Fatigue Short Form 8a** [21]		X	X
Sleep Disturbance Short Form 8a** [21]		X	X
Cognitive Function — Abilities Short Form 8a** [21]		X	X
Self-Efficacy for Managing Chronic Conditions — Managing Symptoms Short Form 8a** [21]		X	X
Ability to Participate in Social Roles and Activities Short Form 8a** [21]		X	X
Pain Interference Short Form 8a** [21]		X	X
Long COVID symptom and impact tools [22]		X	X
Credibility/expectancy questionnaire [23]		X*	
Patient Global Impression of Change scale [24]			X*

^*^Completed by intervention participants only

**Patient-Reported Outcomes Measurement Information System (PROMIS)

### Study setting

This trial aims to enroll and randomize 50 participants who receive care at the UW Post-COVID Rehabilitation and Recovery Clinic within the state of Washington. This is a high-demand outpatient clinic housed within an AMC that has served over 2500 patients since opening in 2020. Assuming a 10% dropout rate, a total of 50 participants will yield 20 completers in each study condition. This sample size was selected to characterize the intervention’s feasibility, acceptability, appropriateness, and preliminary efficacy to inform intervention improvement. A sample size of 20 participants in each condition (accounting for attrition) is appropriate given the specificity of our qualitative research questions [25, 26]. Likewise, this sample size is appropriate for estimating the proportion of participants who rate the intervention as feasible, acceptable, and appropriate. The lower bound of the 95% CI will be above 60% if at least 17 out of 20 (85%) of intervention participants rate the intervention as feasible, acceptable, or appropriate (Supplemental Fig. 1), which is a conservative estimate given satisfaction ratings for similar rehabilitation interventions [27].

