### Randomization and procedures to minimize bias

Participants are randomized using a 1:1 randomization to treatment versus wait-list control condition system. When participants confirm availability for an upcoming clinic group schedule and are confirmed eligible following the re-assessment of Eligibility, participants are 1:1 randomized to either the treatment experimental condition or wait-list control condition. The order of randomization is determined by the order in which participants chronologically completed the re-assessment of eligibility. To minimize bias, the clinicians delivering the intervention are blinded to the research participation status of their group members, as some group members will be enrolled in the study while others will not be. In addition, the REDCap system automatically sends participants baseline and post-treatment/wait-list survey links, where the participant can directly enter their data. As a result, the potential for study staff biases to interfere with data collection is avoided.

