### Data collection procedures and measures

Participants complete self-report measures via REDCap at baseline (prior to starting the treatment/wait-list period) and at post-treatment/wait-list after completing the six-session intervention group or 6-week wait period. For data capture and storage, this study uses REDCap, a secure, password-protected, and HIPAA compliant web-based data platform hosted by the UW Institute of Translational Health Sciences [29, 30].

The primary and secondary outcomes are listed in Table 1. Primary outcomes include the Feasibility of Intervention Measure (FIM), Acceptability of Intervention Measure (AIM), and Intervention Appropriateness Measure (IAM) [20]. Each measure consists of four items that are rated on a 5-point ordinal scale assessing the degree to which an intervention is feasible (e.g., “this intervention seems doable”), agreeable (e.g., “I like this intervention”), or appropriate (e.g., “this intervention seems fitting”). A score greater than 3 (“neither agree nor disagree”) will be used as the cutoff for a dichotomous rating of feasibility, acceptability, and appropriateness. The FIM, AIM, and IAM have shown excellent reliability as well as substantive and discriminant content validity [20]. Secondary outcomes include Patient-Reported Outcomes Measurement Information System (PROMIS) measures of fatigue, sleep disturbance, cognitive difficulties, self-efficacy, pain interference, depression and anxiety symptoms [21], and a long COVID symptom and impact tools measure [22] and Patient Global Impression of Change scale [24].

In addition, participants randomized to the self-management intervention (*n* = 25) complete a 45-minute semi-structured interview with research staff within one month after the final session. The interviewer queries participants about the feasibility, acceptability, and appropriateness of the intervention as well as suggestions for improving the intervention across these areas. Participants are also asked about the perceived efficacy of the intervention and how the intervention could be improved to increase efficacy. Last, the interviewer queries participants’ impressions of the intervention workbook and elicit suggestions for improvement. Data is transcribed via Rev, a secure online transcription service [31].

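### The stated 10% dropout and the stated 20 completers per condition do not agree: 10% of 50 leaves 45 (22 or 23 per condition), and 20 per condition is 20% dropout.

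*Protocol article*

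**What the plan says.** Under Study setting, the protocol article gives the target: "This trial aims to enroll and randomize 50 participants". It then derives the number expected to finish: "Assuming a 10% dropout rate, a total of 50 participants will yield 20 completers in each study condition". Under Randomization and procedures to minimize bias, allocation is equal: "Participants are randomized using a 1:1 randomization to treatment versus wait-list control condition system". The data collection section confirms 25 in the intervention arm: "participants randomized to the self-management intervention (*n* = 25) complete a 45-minute semi-structured interview".

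Study setting uses the figure of 20 in two ways. The first is adequacy for the qualitative questions: "A sample size of 20 participants in each condition (accounting for attrition) is appropriate". The second is precision for the proportion rating the intervention as feasible, acceptable or appropriate: "The lower bound of the 95% CI will be above 60% if at least 17 out of 20 (85%) of intervention participants" give a favourable rating. The text does not name the interval method; it points to a supplemental figure that is not part of the material at hand.

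**The concern.** The sentence gives a total, a dropout rate and a number of completers, and the third does not follow from the first two. Both sizing arguments in that section use the third. A reader cannot tell whether the authors planned for 10% dropout and miscounted the completers, or planned for 20 completers per condition and misstated the rate.

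Two things are at stake. The worked precision example has a denominator that does not match the stated dropout rate. And a later trial that takes its attrition assumption from this pilot's protocol could carry forward a rate that is half of what the completer number implies.

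**Working it through.** **Inputs, all from the protocol article.** Randomized: 50 (Study setting). Allocation: 1:1 (randomization section), so 25 per condition; the data collection section gives 25 for the intervention. Dropout: 10%. Completers: 20 per condition, 40 in total. Precision example: 17 of 20, 95% lower bound above 60%. The text does not say whether the interval is two-sided; I assume that it is.

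**1. The plan's completer number.** Completers = N × (1 − d).

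- At d = 0.10: 50 × 0.90 = 45, or 25 × 0.90 = 22.5 per condition. The stated 40 (20 per condition) is not reproduced, and rounding does not close the gap.
- Dropout implied by 20 per condition: 1 − 40/50 = 0.20.
- In reverse, the number to randomize for 40 completers at 10% is 40/0.90 = 44.4, rounded up to 45. The cruder 40 × 1.10 gives 44. Neither is 50. At 20%, 40/0.80 = 50.

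**2. Readings that could give 20.** Two successive 10% losses give 25 × 0.81 = 20.25. Taking 10% of the total from each condition gives 25 − 5 = 20. The article states neither. It describes the 50 as randomized and the 20 as already allowing for attrition.

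**3. The plan's precision statement at n = 20.** The 95% lower bound for 17/20 is 62.1% (Clopper-Pearson), 64.0% (Wilson), 63.1% (Agresti-Coull), 65.1% (Jeffreys) and 69.4% (Wald). All exceed 60%, so the statement is reproduced. For 16/20 it is 56.3% (Clopper-Pearson) and 58.4% (Wilson), so 17 is the smallest sufficient count by either of these two methods.

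**4. The same statement at 22 or 23 completers.**

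| Count | Proportion | Clopper-Pearson lower | Wilson lower |
|---|---|---|---|
| 17/22 | 77.3% | 54.6% | 56.6% |
| 18/22 | 81.8% | 59.7% | 61.5% |
| 19/22 | 86.4% | 65.1% | 66.7% |
| 17/23 | 73.9% | 51.6% | 53.5% |
| 18/23 | 78.3% | 56.3% | 58.1% |
| 19/23 | 82.6% | 61.2% | 62.9% |
| 20/23 | 87.0% | 66.4% | 67.9% |

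- Read as a proportion: 85% of 22 is 18.7, so at least 19, with a lower bound of 65.1%. 85% of 23 is 19.55, so at least 20, with a lower bound of 66.4%. Both clear 60%.
- Read as a count: 17 fails at both sizes by both methods. The smallest sufficient count is 19/22 or 19/23 by Clopper-Pearson, and 18/22 or 19/23 by Wilson.

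**5. Chance of at least 20 completers among the 25 in a condition.** With independent dropout, P(X ≥ 20) for X binomial(25, 0.90) is 0.97. For X binomial(25, 0.80) it is 0.62.

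**The case against.** The strongest reply is that the mismatch changes nothing of substance, and most of that reply stands. The precision example states its denominator and its percentage, so it is a conditional statement about 17 of 20, not a free-standing target of 17. Put as 85%, it holds at 22 and 23 as well. If the 10% rate is right, the trial will probably end with more completers than it counts on. The study is described as exploratory on efficacy, and the analysis plan attaches no pass or fail decision to the 60% bound.

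A reader might infer more than the article supports, in four ways:

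- **That the precision rule gives a wrong answer if 10% drop out.** It does so only if the 17 is detached from its denominator, which the article does not do.
- **That the completer number and the 17/20 example are the only sizing justification.** Study setting also argues from the specificity of the qualitative questions. That argument cites 20 per condition, and extra completers do not weaken it.
- **That the dropout rate matters because retention is a feasibility benchmark.** No retention threshold is set. Feasibility is judged by the three rating scales, session attendance and the interviews.
- **That the trial is too small.** Nothing in the arithmetic shows this.

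The reply does not remove the error itself: a stated result does not follow from its stated inputs, and the article describes no second stage of loss that would rescue it.

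**Conclusion.** The point holds as a minor inconsistency. The stated inputs give 45 completers, 22 or 23 per condition, against a stated 40, or 20 per condition. The dropout rate that matches 20 per condition is 20%, twice the stated rate.

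The direction matters. If 10% is right, the planning figure is conservative and at least 20 of 25 completing is very likely. If 20% is right, 20 is the expected number and is reached only about six times in ten. This rests on 25 per condition, on the same dropout rate in both, and on independent dropout. The conclusions about the lower bounds also assume a two-sided 95% interval, and the smallest sufficient count at 22 completers depends on the interval method.

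**What to change.** The sponsor should decide which figure was intended and restate the sentence under Study setting. There are two consistent versions:

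1. State 20% dropout, keep 20 completers per condition, and leave the 17 of 20 example as it is.
2. Keep 10% dropout, state 22 or 23 completers per condition, and restate the example count with the interval method named: 19/22 or 19/23 by Clopper-Pearson, 18/22 or 19/23 by Wilson. The statement that 20 per condition already allows for attrition would change with it.

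The article does not show which figure is the slip, so the choice belongs to the authors. In either version the supplemental figure should be checked against the restated denominator. The cost is wording only, with no change to the number randomized, the design or the analysis.

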### Statistical analysis plan

An intent-to-treat (ITT) approach will be used for all quantitative analyses. If participants are missing data at the individual-item level of a multi-item scale, we will impute the missing data using the within-group mean scores for the scale; however, a score will not be imputed if the participant is missing ≥ 40% data in a scale.

First, we will compute descriptive statistics to characterize the sample in terms of demographic and condition-related factors. To assess the first study aim, we will calculate the means and standard deviations of the AIM, IAM, and FIM and quantify the proportion of participants who rate the intervention as feasible, acceptable, and appropriate (average score greater than 3). We will quantify adherence as the percentage of sessions attended out of six sessions. These statistics will be used to contextualize the qualitative results and help inform the extent of modifications necessary to improve the feasibility, acceptability, and appropriateness of the intervention for adults with long COVID.

The second study aim to examine intervention effects is exploratory. We will determine whether randomization was successful by using *t*-tests and chi-square tests to compare the intervention and wait-list groups on a variety of demographic and baseline outcome variables. Any variables that differ between the groups will be included as covariates in the subsequent regression models. After examining randomization, we will explore intervention effects. For the second aim, we will conduct linear regression to assess intervention effects on each outcome (nine models) and will covary for the baseline level of the outcome variable, intervention credibility/expectancy [23], age, sex, and race.

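### The primary AIM/IAM/FIM precision is stated for 20 completers under a blanket ITT promise, so the lower bound above 60% is not assured for the 25 randomized to the intervention

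*Protocol article*

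**What the plan says.** All references are to the protocol article.

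- **Study setting.** Fifty participants are to be randomized. The section then states: "Assuming a 10% dropout rate, a total of 50 participants will yield 20 completers in each study condition". The only precision statement for the primary outcomes uses that 20: the 95% lower bound is said to exceed 60% "if at least 17 out of 20 (85%) of intervention participants rate the intervention as feasible, acceptable, or appropriate".
- **Data collection procedures and measures.** The intervention arm has 25 participants. AIM, IAM and FIM have four items each. The post-treatment survey is placed "after completing the six-session intervention group or 6-week wait period".
- **Table 1.** AIM, IAM and FIM are collected once, at t1, in the intervention arm only.
- **Statistical analysis plan.** "An intent-to-treat (ITT) approach will be used for all quantitative analyses". Missing items are imputed, but no score is imputed once 40% or more of a scale is missing. The primary summary is the proportion with a mean score above 3. Its denominator is given only as participants. Adherence is the percentage of the six sessions attended.
- **Randomization and procedures to minimize bias.** REDCap sends the survey links automatically. No attendance condition is mentioned.

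**The concern.** The sizing expects five of the 25 intervention participants to be lost. Because the primary measures have no earlier assessment, someone who returns nothing at t1 has no primary outcome, and the stated rules give no way to count that person. The primary proportion would then be a respondent proportion carrying an intent-to-treat label.

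This matters because the article uses these figures to judge how much modification the program needs. People who leave may be those who found it least doable or acceptable. If so, the respondent proportion is too high, and a lower bound above 60% would be read as applying to everyone offered the program when it applies only to those who answered.

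**Working it through.** **Inputs.** 25 randomized to the intervention (Data collection procedures and measures); 20 completers per arm, 10% dropout and 17 of 20 endorsing (Study setting); ITT and the 40% rule (Statistical analysis plan). The interval method is not named in the text, so two-sided 95% exact (Clopper-Pearson) and Wilson intervals are both shown.

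**1. The plan's own figure.** 17/20 = 85%. The lower bound is 62.1% exact and 64.0% Wilson. 16/20 gives 56.3% exact and 58.4% Wilson. So 17 is the correct minimum for n = 20 by either method, and the statement reproduces.

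**2. What the missing-data rule does.** With four items per measure, one missing item is 1/4 = 25% and can be imputed. Two missing items are 2/4 = 50%, and a wholly missing measure is 100%; neither is scored.

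**3. The same result over all 25.** Take 17 endorsements among 20 respondents and let k of the 5 without a rating be endorsers. The proportion is (17 + k)/25.

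| k | Proportion | Exact lower bound | Wilson lower bound |
|---|---|---|---|
| 0 | 17/25 = 68% | 46.5% | 48.4% |
| 1 | 18/25 = 72% | 50.6% | 52.4% |
| 2 | 19/25 = 76% | 54.9% | 56.6% |
| 3 | 20/25 = 80% | 59.3% | 60.9% |
| 4 | 21/25 = 84% | 63.9% | above 60% |
| 5 | 22/25 = 88% | 68.8% | 70.0% |

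The bound stays above 60% only if at least 4 of the 5 (exact) or 3 of the 5 (Wilson) would have endorsed. Equivalently, n = 25 needs 21/25 by the exact method or 20/25 by Wilson.

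**4. The dropout figure.** 50 × 0.90 = 45, or 22 to 23 per arm. Twenty of 25 is a loss of 5/25 = 20%. Forty completers at 10% loss would need 40/0.90 = 44.4, so 45 randomized. The 10% and the 20 per arm do not match.

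**5. Does the point depend on a 20% loss?** At about 10% loss there would be 22 or 23 respondents. The exact minimum for 22 is 19/22 (lower bound 65.1%). Over 25 this runs from 19/25 (54.9%) to 22/25 (68.8%). The exact minimum for 23 is 19/23 (61.2%), which runs from 19/25 (54.9%) to 21/25 (63.9%). The range narrows but still crosses 60%.

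**The case against.** Sizing on the expected evaluable number is ordinary practice. It does not define an analysis set and does not by itself contradict ITT. No sentence restricts the primary proportion to completers. The wording about completing the six-session group can be read as timing, parallel to the six-week wait, and the automatic links suggest that someone who stops attending may still be surveyed. How to treat a wholly missing score is often left to a fuller plan.

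Most of this stands, and it limits the point. Four stronger readings are tempting, and the documents do not support them:

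- **That dropouts are removed from the denominator.** The article does not fix the denominator. Their loss follows from the stated rules; it is not itself a stated rule.
- **That the 60% bound fails for those randomized.** That holds only if enough of those without ratings are non-endorsers. 17/25 is the worst case, and the documents give no data on how leavers would rate the program.
- **That 60% is a success criterion to be replaced by 21 of 25.** It illustrates precision. The article attaches no decision to it.
- **That the attendance hypothesis needs a single floor.** The 43–93% band is wide (0.43 × 6 = 2.6 sessions at its lower end), but its width has no bearing on who is counted. Adherence under ITT is most naturally averaged over everyone randomized; the article need only say so.

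What remains does not rest on an omission. The article has its own statistical analysis section, which sets ITT without exception and a missing-data rule. Those two statements and the completer-based precision figure are not reconciled.

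**Conclusion.** The concern holds as a mismatch between stated items. The 17/20 statement is arithmetically right but describes respondents. For the 25 randomized, a lower bound above 60% is possible but not assured: the exact bound lies between 46.5% and 68.8%, and the point estimate between 68% and 88%, against a stated 85%. These ranges assume 20 respondents with 17 endorsing. The direction of any bias rests on the further assumption that people who leave are less favorable, which is reasonable in a feasibility trial but untested here.

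The 10% dropout and the 20 completers per arm contradict each other whatever is decided about the denominator.

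**What to change.** 1. Confirm that the t1 survey goes to all participants randomized to the intervention, regardless of attendance.
2. Report each AIM, IAM and FIM proportion over all 25 randomized, with non-response counted as not endorsing and labelled as the conservative bound, beside the respondent-only proportion.
3. Label the 17/20 statement as applying to respondents. Add the figure for 25 with the interval method named (21/25 exact, lower bound 63.9%; or 20/25 Wilson, 60.9%), presented as a precision illustration and not as a success rule.
4. State that attendance is computed over all randomized to the intervention.
5. Reconcile the 10% dropout with 20 completers per arm.

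These are wording and reporting changes: no new participants, visits or measures. The downside is a less favorable headline figure.
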